### Data analyses

2.6

All the studied variables will be descriptively analyzed by means (SDs), medians (ranges) or n (percentages). Between groups baseline differences will be tested using 2-tailed t-test, Man-Whitney test or chi-square/Fisher’s exacts test based on the type of variables compared.

Despite the trial being exploratory study, data will be analyzed following the intent-to-treat and/or completer strategies, based on the presence of drop-out. The first hypothesis (H1) will be tested using an independent two-way repeated measures analysis of variance (ANOVA) with 3 levels for each factor (Group: A-MR *vs* MR *vs* NT; Time: pre-treatment *vs* post-treatment *vs* follow-up) and/or Linear Mixed Models (LMM) for each primary and secondary outcome studied. The LMM will be used to analyze the possible effect of between groups differences at baseline measures as covariables, and to analyze the effect of the presence PGD diagnoses following the ICD-11 duration criterion at baseline. Bonferroni corrections will be applied to all analyses, and partial eta-square and Cohen’s *d* effect sizes will be calculated for interaction effects and for between- and within-group comparisons, respectively. Confidence intervals for Cohen’s *d* will be estimated at a 95% confidence level and 500 bootstrap samples.

The analysis of the second hypothesis (H2) will be based on the outcomes of testing H1, with reduction in grief severity (TRIG and TGI scores) as the dependent variable for mediation analyses. The mediation model will include all participants in the study and will only incorporate the potentially significant mediating variables (meaning-made, psychological flexibility, and self-belief consistency) identified in previous analyses. Power analyses for the mediation models will also be conducted based on a Monte Carlo simulation.

The statistical analyses will be conducted using R version 4.2.3 (79). The following R packages will be used for data exploration, description, and preprocessing if necessary: tidyverse (80), car (81), moments version 0.14.1 (82), and nortest version 1.0-4 (83). The repeated measures ANOVAs and/or Lineal Mixed Models will be conducted using rstatix package version 0.7.2 (84). Finally, the mediation model will be tested using the lavaan package version 0.6-12 (85) and statistical power for the mediational analysis will be calculated using WebPower package version 0.9.4 (86).

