### Study design and hypotheses

2.1

This three-arm, non-randomized controlled trial investigates the efficacy of Ayahuasca-assisted Meaning Reconstruction therapy (A-MR) in decreasing normal and pathological grief symptoms in people who have lost a first-degree relative within the prior 12 months. Participants are sequentially allocated to the following treatment conditions: (1) a control group receiving Meaning Reconstruction therapy (MR), (2) a control group receiving No Treatment (NT), and (3) an experimental group receiving Ayahuasca-assisted Meaning Reconstruction therapy (A-MR).

The objective of this trial is two-fold. First, our aim is to compare the efficacy of A-MR with that of MR and NT by assessing differences in (a) the severity of normal grief symptoms, (b) pathological grief symptoms, (c) quality of life, and (d) posttraumatic growth. Moreover, we are also interested in analyzing how each condition may influence the proposed processes of change: (e) meaning-made (f) psychological flexibility, and (g) self-belief consistency. Additionally, we will explore the participants’ (h) subjective effects of ayahuasca and the (i) acceptance-avoidance promoting effects.

The following hypothesis will be tested:

Hypothesis 1. The experimental group receiving A-MR will show greater improvement in normal and pathological grief symptoms, quality of life, and post-traumatic growth compared to both control groups (MR and NT), at post-treatment and 3 months follow-up. Moreover, MR group will show greater improvement than the NT group, expecting a medium clinical effect size.

Hypothesis 1.1. The experimental group receiving A-MR will show greater improvement in psychological flexibility, meaning-made, and self-believed consistency compared to both control groups (MR and NT), at post-treatment and 3 months follow-up. Furthermore, MR will also show greater improvement than the NT group, expecting a medium clinical effect size.

Hypothesis 2. Reductions in the severity of normal and pathological grief symptoms will be principally related to changes in meaning- made, but also to changes in psychological flexibility and self-belief consistency. Moreover, a stronger relationship between changes in the severity of grief symptoms and meaning-made is expected in the A-MR group.

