### Participants

2.2

Participants eligible for this study will be English and Spanish-speaking adults experiencing grief symptoms due to the death of a loved one. Inclusion criteria involve: (1) people aged 18-65; (2) having experienced the loss of a first-degree relative; (3) within the past 12 months; and (4) with a Texas Revised Inventory of Grief score over 39 (TRIG ≥ 40). Exclusion criteria involve: (1) medically and mentally significant health conditions; (2) history of psychotic disorder (Axis I- DSM-IV-TR); (3) pregnant or breastfeeding women; (4) hypertension (SBP > 140 mmHg, DBP > 90 mmHg, HR >100 bpm); (5) substance use disorder, excluding nicotine; (6) alcohol consumption exceeding 40g/day; (7) concurrent psychological or pharmacological treatment for grief. Those who are not eligible will be referred to other mental health professionals specialized in bereavement.

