### Sample size

2.4

Given that no comparative trials analyzing the therapeutic effect of PAP on reduction of grief symptoms has been published to date, sample size was calculated based on the results of González et al. (35) observational study. The observed Cohen’s d (0.84) for the study group between the baseline and the 15^th^-day-post-treatment assessment, and TRIG measurement correlation of 0.55, were used to estimate the sample size for this study. Therefore, sample size was calculated based on the assumption of a between groups differences at post-treatment of at least 9.4 points (TRIG score) in mean change between the A-MR and the NT groups. Sample size with power of 0.90 and an alpha of 0.05 was calculated using pwrss R package version 0.3.1 (58). To find at least the above effect size, a total sample of 69 participants is needed, but as drop-out rate of 20% were considered, 84 participants will be recruited.

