## Discussion

3

This clinical trial is the first to examine the potential of psychedelic-assisted grief therapy and, more specifically, of ayahuasca-assisted meaning reconstruction therapy for the reduction of the severity of grief symptoms. The study also investigates whether the intervention promotes quality of life and post-traumatic growth, while exploring a series of processes of change that may mediate this therapeutic effect. If this intervention proves to be both feasible and effective upon completion of this study, a future clinical trial will be designed with a focus on (a) prioritizing the mechanism(s) of change that will be identified through mediation analyses.

A key limitation of the trial is that the sequential allocation of participants may have a bias influence on the outcomes. Another limitation is a threat to external validity connected to the recruitment process: the self-referral process relies on the social media presence of psychedelic research and education institutions and associations, which may limit the generalizability of the clinical outcomes to the general population. Moreover, the fact that ayahuasca is a plant concoction complicates the determination of which alkaloids and active compounds influence the outcomes. Finally, accepting bereaved people who meet the ICD-11 sixth-month-since-the-loss criterion for PGD disorder (instead of the more conservative 12-month criterion) could blur the distinction between prevention and treatment. Nevertheless, we will also analyze PGD criteria following the ICD-11 as a potential moderator.

Given the lack of grief literacy in the general population, the widespread loneliness in Western society, and lack of mental health support during the early stages of bereavement, it is imperative to improve bereavement support for acute grief (13). The scarcity of evidence-based therapies for the prevention of PGD indicates the urgent need for new interventions to support bereaved people at moderate-to-high risk, according to the four-tier model (116). We anticipate that the outcomes of this trial will significantly contribute to the field of bereavement care, helping to reduce the time needed for the bereaved to receive evidence-based support, and promoting their adaptation. Moving beyond the context of grief and loss, this study will also contribute to advancing our understanding of PAP as way to prevent and reduce the global mental health burden (14).

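### If baseline covariables enter the LMM as main effects, as the wording ordinarily means, they cannot adjust the Group x Time contrasts that test H1

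*Protocol article*

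**What the plan says.** Section 2.6 (Data analyses) tests H1 with a three-level Group factor and a three-level Time factor, by repeated-measures ANOVA or a mixed model: "Time: pre-treatment *vs* post-treatment *vs* follow-up) and/or Linear Mixed Models (LMM) for each primary and secondary outcome studied". Pre-treatment is therefore one of the outcome levels. On baseline imbalance the section says: "The LMM will be used to analyze the possible effect of between groups differences at baseline measures as covariables". On reporting it says that "effect sizes will be calculated for interaction effects and for between- and within-group comparisons".

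H1 itself (section 2.1) is worded as greater improvement in A-MR than in MR and NT at post-treatment and at 3-month follow-up, which is a statement about change. Section 2.1 also says "Participants are sequentially allocated to the following treatment conditions", and section 3 (Discussion) names as a key limitation that "the sequential allocation of participants may have a bias influence on the outcomes". The article states no other analytic measure against baseline imbalance. It writes out no model equation and does not mention a covariable x Time term.

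**The concern.** In a model where the pre-treatment score is a response, a treatment effect on improvement sits in the Group x Time interaction. A covariable entered as a main effect acts on a person's overall level and not on change. It can correct a comparison of levels, but not the comparison that H1 makes.

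This matters more here than in a randomized trial. The arms are filled in sequence, so they may differ on factors that predict how fast grief eases. Months since the loss is an obvious candidate, since entry is open to anyone bereaved within the past 12 months. If such a factor is measured and put in the model as a main effect, the adjusted H1 contrast is the unadjusted one under another label. The problem is separate from which covariables are chosen: it applies even when the right ones are in the model.

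**Working it through.** **Inputs.** From section 2.4 (Sample size): Cohen's d 0.84, difference in mean change 9.4 TRIG points, correlation between TRIG measurements 0.55, 69 analysable participants (23 per arm). The SD is not stated; 9.4/0.84 = 11.2 is assumed. SD of change = 11.2 x sqrt(2 x (1 - 0.55)) = 10.6. The imbalance between arms and the covariable-change correlation are not in the documents and are assumed as ranges.

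The point itself rests on no stated figure. As a check on the inputs, d on the change scale is 0.84/sqrt(0.90) = 0.885, and a one-sided 5% two-sample t-test with 90% power then needs 23 per arm, or 69 in all. So a change-score reading fits the plan's own sample size.

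**Step 1: algebra.** With main effects only, for person i in group g at time t,

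Y(i,t) = Group(g) + Time(t) + GroupTime(g,t) + b X(i) + u(i) + e(i,t).

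The change to T3 is

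Y(i,T3) - Y(i,T0) = [Time(T3) - Time(T0)] + [GroupTime(g,T3) - GroupTime(g,T0)] + [e(i,T3) - e(i,T0)].

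Both b X(i) and u(i) drop out. If the covariable has its own coefficient at each time, the term [b(T3) - b(T0)] X(i) stays in the change and is adjusted for.

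**Step 2: fitted models.** Simulated three-arm, three-visit data, 23 per arm, random-intercept LMM, complete data. A-MR vs NT Group x Time estimate (SE):

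| Model | Data set 1 | Data set 2 |
|---|---|---|
| No covariable | -4.764 (2.857) | -3.834 (3.116) |
| Covariable as main effect | -4.764 (2.857) | -3.834 (3.116) |
| Covariable x Time | -2.985 (2.939) | -0.247 (3.324) |

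Baseline TRIG entered as a main effect also left the estimate unchanged. In an example with 20% drop-out, the estimates without and with the main effect were -3.59 and -3.58. In a separate set of simulations with baseline score as the covariable, the estimate moved by 0.000 in every complete-data replicate. With 20% drop-out it moved by at most 0.05 points on average, and by 1.0 in the most extreme single replicate.

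**Step 3: possible size.** With no treatment effect, bias = correlation x imbalance (in SD) x SD of change. The standard error of a two-arm difference in change is 10.6 x sqrt(2/23) = 3.13. Rejection rates come from the noncentral t with 44 df, noncentrality = bias/3.13. The 1.67% level is 5%/3, assuming three pairwise contrasts. About 0.59 SD is the smallest imbalance that a two-sided 5% t-test would flag at 23 per arm, since 2.015 x sqrt(2/23) = 0.594.

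| Correlation | Imbalance | Bias (TRIG points) | Two-sided 5% | Two-sided 1.67% |
|---|---|---|---|---|
| 0.2 | 0.6 SD | 1.27 | 6.8% | 2.5% |
| 0.2 | 0.8 SD | 1.70 | 8.3% | 3.3% |
| 0.3 | 0.6 SD | 1.91 | 9.2% | 3.7% |
| 0.3 | 0.8 SD | 2.55 | 12.5% | 5.5% |

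Simulation of the same cells at 5% gave 7-13% with the main effect, and 4.5-5.5% once covariable x Time was included.

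**The case against.** The strongest objection is that the article specifies no such model. It gives no equation and no list of fixed effects. The three Time levels are written beside the ANOVA and reach the LMM only through the and/or. Covariable x Time terms are not ruled out, and detail of this kind is often left to an analysis plan. This stands as far as it goes: a reader might infer that the plan excludes interactions, and the text does not say so. But the article does state the Time levels, the emphasis on the interaction and the role of the covariables. On the ordinary meaning of those words, the adjustment cannot reach H1.

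A reader might also infer that the adjustment does nothing at all. It does not follow. Between-group comparisons are planned as well, and a main effect does shift adjusted contrasts in level at T3 or T4.

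Third, the plan is not confined to main effects of baseline factors. Section 2.6 will examine PGD status under the ICD-11 duration criterion, and the Discussion calls it a potential moderator. With a six-month minimum, that status partly reflects time since loss. This is a real but partial mitigation: it is one dichotomised, diagnosis-based variable and does not cover the other covariables.

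Fourth, a reader might take 7-13% as the trial's error rate. The imbalance and the correlation are assumed, and section 2.6 plans Bonferroni corrections, so fewer false positives would be declared than an uncorrected 5% implies. The excess over the nominal level remains at either threshold.

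Finally, that the result would be presented as fully corrected is conjecture. The article calls the study exploratory and discloses the allocation problem.

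**Conclusion.** The point holds conditionally. If baseline differences enter the LMM as main effects, the Group x Time contrasts that test H1 are not adjusted for them: exactly so with complete data, very nearly so with drop-out. That conclusion is algebraic and needs no assumption about effect sizes.

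The size of any harm does rest on assumptions. With SD 11.2, r = 0.55, 23 per arm, an imbalance of 0.6-0.8 SD and a covariable-change correlation of 0.2-0.3, the bias is 14-27% of the planned 9.4-point difference (1.27/9.4 to 2.55/9.4). Error rates rise to roughly 1.4 to 2.5 times nominal at 5% (6.8/5 to 12.5/5). With little imbalance, or a factor unrelated to change, the harm would be negligible. The documents do not show that the trial will be biased to this extent. They show that the stated adjustment, on its ordinary reading, would not remove such bias if it arose.

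**What to change.** In the LMM for each primary and secondary outcome, enter each baseline covariable, including months since loss, together with its interaction with Time. Equivalently, model T3 and T4 change with the covariables in the model. Report the A-MR vs MR and A-MR vs NT contrasts at T3 and T4 from that model.

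Treat adjustment for the outcome's own baseline score as a sensitivity analysis. It removes regression to a common mean, but it can bring its own bias if non-randomized arms come from populations with different stable levels.

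The cost is one line of model specification, two degrees of freedom per covariable and a slightly larger standard error: about 3% in the first data set (2.939/2.857) and 7% in the second (3.324/3.116). The change deals with measured confounders only; unmeasured consequences of sequential allocation remain a limitation.

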**Method:**

The outlined protocol is a three-arm, non-randomized controlled trial focused on reducing normal and pathological grief symptoms, comparing the effectiveness of Ayahuasca-assisted MR therapy (A-MR), MR therapy alone (MR) and No Treatment (NT). At least 69 people who lost a first-degree relative during the prior year, and with a Texas Revised Inventory of Grief score up 39 (TRIG ≥ 40), will participate in the trial. Participants will be allocated to an A-MR (n ≥ 23), MR (n ≥ 23) or NT (n ≥ 23) group. Those from the A-MR and MR therapy groups will undergo a therapeutic process involving 9 sessions of online psychotherapy. In addition, the A-MR condition involves 2 group sessions of ayahuasca. The primary outcomes will be normal and pathological grief severity as measured by the TRIG and Traumatic Grief Inventory Self-Report (TGI-SR), administered at baseline, post-treatment, and 3-month follow up. Measures of quality of life, post-traumatic growth, meaning-made, psychological flexibility, and self-belief consistency will be also included. In addition, subjective effects of ayahuasca and acceptance-avoidance promoting effects will be assessed following ayahuasca administration. Finally, we will analyze the potential mediating effect of meaning-made, psychological flexibility and self-belief consistency in grief symptoms (as measured by the TRIG and TGI).

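### Allocation is sequential, yet covariate adjustment appears to depend on which baseline differences are observed, in a mixed model that is itself optional

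*Protocol article*

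**What the plan says.** All references are to the protocol article.

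- Section 2.1 (Study design and hypotheses): "Participants are sequentially allocated to the following treatment conditions". The design is declared non-randomized.
- Section 3 (Discussion) gives as a key limitation that "the sequential allocation of participants may have a bias influence on the outcomes".
- Section 2.6 (Data analyses), first paragraph: "Between groups baseline differences will be tested using 2-tailed t-test, Man-Whitney test", with chi-square or Fisher tests for categorical variables.
- Section 2.6, second paragraph: "The LMM will be used to analyze the possible effect of between groups differences at baseline measures as covariables". The same sentence adds one factor named in advance, PGD diagnosis by the ICD-11 duration criterion; the Discussion calls it a potential moderator.
- H1 is tested by repeated-measures ANOVA and/or an LMM, with three groups and three time points, so the baseline score enters as one level of Time. Bonferroni correction applies to all analyses.
- Abstract, Method: "Participants will be allocated to an A-MR (n ≥ 23), MR (n ≥ 23) or NT (n ≥ 23) group". Section 2.4 (Sample size): "a total sample of 69 participants is needed, but as drop-out rate of 20% were considered, 84 participants will be recruited".

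**The concern.** Without randomization, baseline adjustment has to carry much of the case that the arms are comparable. Section 2.6 appears to let the observed data decide what is adjusted for. That causes two problems. With arms of 23 to 28, an imbalance large enough to matter will often not be flagged, and a non-significant difference does not show that the arms are balanced. The final model also becomes dependent on the data. In addition, because of the and/or wording, an unadjusted ANOVA could stand as the H1 result. Months since loss illustrates the point. Eligibility spans the whole first year of bereavement, and arms filled in sequence could differ on it. It is covered in advance only through the dichotomous PGD diagnosis.

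**Working it through.** **Inputs from the protocol article.** At least 23 per arm; 84 recruited, which is 84 / 3 = 28 per arm if equal; power 0.90; alpha 0.05; d = 0.84; TRIG correlation 0.55; planned difference 9.4 TRIG points. Implied SD = 9.4 / 0.84 = 11.19 points.

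**Assumptions not in the documents.** A true baseline imbalance of 0.4 SD (0.2 to 0.8 also shown), a confounder-outcome correlation of 0.3 to 0.5, and significance at 0.05 as the entry rule.

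**1. The plan's own figure.** The standardised effect on change scores is 0.84 / √(2 × (1 − 0.55)) = 0.885. A one-sided two-sample t-test at alpha 0.05 and power 0.90 then needs 23 per arm, or 69 in total, which matches. Two-sided versions give 22 (ANCOVA), 28 (change score) or 31 (raw score) per arm. Section 2.4 does not state sidedness. Here this only confirms the arm size. Also 23 × 1.2 = 27.6, rounded up to 28, and 3 × 28 = 84.

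**2. Chance that one pairwise test flags the imbalance.** Two-sided t-test, noncentrality = δ × √(n / 2), df = 2n − 2.
- n = 23, δ = 0.4: noncentrality 0.4 × √11.5 = 1.36, power 0.264, so 74% missed.
- n = 28, δ = 0.4: noncentrality 0.4 × √14 = 1.50, power 0.312, so 69% missed.
- n = 23 at other sizes: 90% missed at 0.2 SD, 83% at 0.3, 62% at 0.5, 49% at 0.6, 24% at 0.8.
- Mann-Whitney by simulation at n = 23, δ = 0.4: power about 0.25.
- Per-arm size for 80% power at 0.4 SD: 2 × (1.960 + 0.842)² / 0.4² = 98.1, so about 99, against 23 to 28 planned.

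**3. Three arms.** Simulation of 20,000 trials, with one arm 0.4 SD away from the two others.

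| Trigger for adjustment | Missed, n = 23 | Missed, n = 28 |
|---|---|---|
| Any pair, uncorrected | 59% | 53% |
| Any pair, Bonferroni over three | 76% | 72% |
| Three-group F-test | 74% | 69% |

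**4. Bias if the imbalance is missed.** H1 concerns group by time, so what matters is the bias in change from baseline. With similar SDs at both times, bias ≈ δ × (r_post − r_pre) × SD, where r_post and r_pre are the confounder's correlations with the post-treatment and baseline scores.
- r_pre = 0, r_post = 0.3: 0.4 × 0.3 × 11.19 = 1.3 points, 14% of 9.4.
- r_pre = 0, r_post = 0.5: 0.4 × 0.5 × 11.19 = 2.2 points, 24% of 9.4.
- r_pre = 0.3, r_post = 0.5: 0.4 × 0.2 × 11.19 = 0.9 points, about 10% of 9.4.
- r_pre = r_post: 0.

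For these correlations, and with r_pre and r_post of the same sign, 1.3 to 2.2 points is therefore an upper range, reached only by a confounder unrelated to baseline grief.

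**The case against.** The strongest objection is that Section 2.6 never says the baseline tests choose the covariates. The tests and the LMM stand in separate sentences, with no cut-off. This stands as a limit: the link is the natural reading, not a stated rule, and the miss rates hold only if the rule is significance at 0.05. Without any rule, the choice is more open still.

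A covariate list also commonly belongs in an analysis plan or full protocol, which is not shown. Its absence is not the point here. The point is that the article does describe how covariates arise, and the method described depends on the data.

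A reader might go further in four ways that the documents do not support.
- **That this adjustment is the only defence.** The baseline score of each outcome is already a Time level, and PGD status by the ICD-11 criterion, which depends partly on time since loss, is analysed whatever the tests show. The protection is coarse, but it exists.
- **That a 1.3 to 2.2 point bias is to be expected.** That treats the contrast as an unadjusted post-treatment comparison. Under group by time it is an upper range.
- **That about three in four confounders go unnoticed.** That figure belongs to one pair, 23 per arm and an assumed 0.4 SD.
- **That two-group tests are invalid with three arms.** Pairwise tests with the stated Bonferroni correction are valid, and chi-square and Fisher tests can take three groups.

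The protocol also discloses the allocation limitation and calls the trial exploratory. That is fair, but disclosure does not repair the adjustment method.

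**Conclusion.** The point holds in a limited form. In a sequentially allocated trial, the article on its natural reading ties adjustment to observed baseline differences and leaves the adjusted model optional, with one factor named in advance. If p < 0.05 is the screen, a 0.4 SD imbalance goes unflagged in roughly half to three quarters of cases: 53 to 59% under the most lenient three-arm trigger, 69 to 76% under a single pairwise test, an F-test or Bonferroni-corrected pairs. The resulting bias lies between zero and about 2.2 TRIG points for the assumed 0.4 SD and correlations up to 0.5, depending on how far the confounder predicts change and not merely level. The imbalance, the correlations and the entry rule are assumptions. That adjustment follows the observed differences does not depend on the first two. The weakness bears on all H1 contrasts and can be mended before analysis.

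**What to change.** - Make the adjusted LMM the primary H1 analysis, removing the and/or choice.
- Fix the covariates before analysis and use them whatever the baseline comparisons show: baseline score of the outcome, months since loss as a continuous variable, age, and kinship to the deceased. Age, date of loss, kinship and TRIG all bear on eligibility, so little or no new data collection should be needed.
- Specify the model so that adjustment reaches the contrast. Either T3 and T4 are the responses with the baseline score as a covariate, or, if baseline stays a Time level, each other covariate also interacts with time. A covariate entered only as a main effect shifts all time points alike and, with complete data, leaves the group-by-time estimate unchanged.
- Report baseline by arm with standardised differences, and do not use significance tests to choose covariates.
- Report the time from T0 to T3 by arm, but do not adjust for it: it arises after allocation and may depend on the arm.

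The cost is a few degrees of freedom and a change of wording. For the listed factors, selection by test no longer occurs. Unmeasured confounding remains and should stay among the stated limitations.

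### With 500 bootstrap samples, the 95% limits for between-group Cohen's d carry avoidable seed-to-seed noise (Monte Carlo SD about 0.03 to 0.04)

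*Protocol article*

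**What the plan says.** Section 2.6 (Data analyses) plans Cohen's d for between- and within-group comparisons and partial eta-squared for interaction effects. The confidence intervals for d "will be estimated at a 95% confidence level and 500 bootstrap samples". Hypothesis 1 is tested by a two-way repeated-measures ANOVA and/or linear mixed models for each outcome, and "Bonferroni corrections will be applied to all analyses". The same section calls the trial exploratory.

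Two other sections set the scale. Section 2.1 predicts that MR will improve more than NT, "expecting a medium clinical effect size", without giving a number. Section 2.4 plans the A-MR versus NT contrast from a Cohen's d of 0.84 and a "TRIG measurement correlation of 0.55", and concludes that "a total sample of 69 participants is needed, but as drop-out rate of 20% were considered, 84 participants will be recruited".

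**The concern.** A 95% bootstrap limit is a tail quantile of the resampled estimates. With 500 resamples it is read off from roughly the dozen most extreme values on each side. A second run on the same data with another seed gives different limits, through simulation noise alone.

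What is at stake is the precision and reproducibility of a reported result. A reader who sees limits for d to two decimals would assume that they are determined by the data. Here the second decimal, and sometimes the first, partly reflects the seed. If a lower limit happens to fall near zero, the seed can also settle which side of zero it lands on. The number of resamples is a value that the article states, so this is not a detail left to a fuller document.

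**Working it through.** **Inputs**
- Resamples and level: 500 and 95% (Section 2.6).
- Per-arm size: 23 (Abstract; 69/3 from Section 2.4), or 28 if the 84 recruited are split equally and all retained (84/3; the equal split is an assumption).
- Effect: 0.84 (Section 2.4). "Medium" is taken as d = 0.5, which is an assumption; 0.6 and 0.65 were also run.
- Pre-post correlation: 0.55 (Section 2.4), used for within-group d only.
- Assumed: percentile bootstrap, normal-shaped data, d standardised by the pooled SD.

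**Step 1. Reproduce the plan's sample size, which sets the n for the bootstrap.** On change scores the effect is 0.84/√(2(1 − 0.55)) = 0.84/√0.9 = 0.885. A one-sided two-sample t-test at 0.05 with power 0.90 needs 22.56, so 23 per arm and 69 in total, as stated. (Section 2.4 does not state sidedness; the one-sided change-score test is the variant that matches.) For recruitment, 23 × 1.2 = 27.6, rounded to 28, and 3 × 28 = 84.

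**Step 2. Resamples per tail.** 500 × 0.025 = 12.5.

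**Step 3. Analytic Monte Carlo error of a limit.** SD = √(0.025 × 0.975/B) / f(q), where f(q) is the density of the bootstrap distribution at the limit, approximated by φ(1.96)/SE(d), and SE(d) = √(2/n + d²/(4n)).
- n = 23, d = 0.5: SE = √(0.0870 + 0.0027) = 0.2995; f = 0.0584/0.2995 = 0.195; SD = 0.00698/0.195 = **0.036**.
- n = 28, d = 0.5: SE = √(0.0714 + 0.0022) = 0.2714; f = 0.0584/0.2714 = 0.215; SD = 0.00698/0.215 = **0.032**.

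**Step 4. Simulation.** 200 seeds on each of 12 data sets scaled to an exact observed d, B = 500. Paired entries are lower/upper limit.

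| n per arm | observed d | mean limits | Monte Carlo SD | band holding 95% of seeds | mean gap, two seeds | seeds with lower limit above 0 |
|---|---|---|---|---|---|---|
| 23 | 0.5 | −0.065, 1.165 | 0.034/0.043 | 0.130/0.165 | 0.038/0.047 | 1–6% |
| 23 | 0.6 | 0.043, 1.236 | 0.034/0.040 | 0.133/0.153 | 0.038/0.046 | 86–94% |
| 23 | 0.65 | 0.097, 1.280 | 0.034/0.040 | 0.135/0.153 | 0.038/0.045 | 98–100% |
| 23 | 0.84 | 0.280, 1.545 | 0.035/0.045 | 0.137/0.170 | 0.039/0.050 | 100% |
| 28 | 0.5 | −0.009, 1.073 | 0.031/0.036 | 0.122/0.140 | 0.035/0.041 | 28–56% |
| 28 | 0.6 | 0.095, 1.172 | 0.031/0.037 | 0.118/0.138 | 0.035/0.042 | 98–100% |
| 28 | 0.84 | 0.333, 1.447 | 0.030/0.038 | 0.116/0.145 | 0.034/0.043 | 100% |

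The simulated SDs are close to Step 3. For the lower limit, 1.96 × 0.034 = 0.067, so the seed matters for zero only when that limit lies within about 0.07 of it.

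**Step 5. How often that happens.** Over 300 simulated trials with 23 per arm, two seeds disagree about zero in about 4% of trials when the true d is 0.5, and in about 2.5% when it is 0.84.

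**Step 6. Within-group d** (n = 23, r = 0.55, d = 0.5): limits 0.18 to 0.93, Monte Carlo SD 0.019/0.029, bands 0.07/0.11. Zero is not in play.

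**Step 7. More resamples** (n = 23, d = 0.5):

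| B | Monte Carlo SD | band holding 95% of seeds |
|---|---|---|
| 500 | 0.033/0.039 | 0.132/0.148 |
| 2,000 | 0.019/0.020 | 0.070/0.075 |
| 5,000 | 0.011/0.014 | 0.040/0.052 |
| 10,000 | 0.008/0.011 | 0.031/0.042 |

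The error falls with √B: √(10,000/500) = 4.5, and 0.036/4.5 = 0.008.

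**The case against.** The main defence is that nothing in the trial turns on these intervals. Hypothesis 1 is decided by ANOVA and/or a mixed model, the trial is described as exploratory, and no section makes exclusion of zero a criterion. The noise is also small beside the sampling uncertainty: at 23 per arm and d = 0.5 the interval is about 1.23 wide (1.165 + 0.065), so an SD of 0.034 is under 3% of it. All of this stands, and it keeps the point minor.

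It also rules out several stronger readings:
- A reader might infer that a limit usually shifts by 0.1 to 0.2 from run to run. That is the spread over nearly all seeds; the usual gap between two runs is 0.04 to 0.05.
- A reader might infer that the seed decides whether a medium effect excludes zero. At 23 per arm and an observed d of 0.5, 94–99% of seeds agree that zero is included; at an observed 0.84 every seed excludes it. Only a lower limit close to zero is exposed, as at d = 0.5 with 28 per arm.
- A reader might treat these intervals as the trial's main measure of effect. Section 2.6 also plans partial eta-squared, and Section 2.4 expresses the target as 9.4 TRIG points.
- A reader might see an error in keeping 95% intervals beside Bonferroni-corrected tests. Unadjusted intervals for descriptive effect sizes are a legitimate choice, and Section 2.6 does not define the Bonferroni family, so any matched level would be assumed.

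The bootstrap type and the seed are details that an article may leave to a fuller document, so their absence is no fault. What the defence does not answer is the stated number: 500 is low for 2.5% tail quantiles, and raising it costs practically nothing.

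**Conclusion.** The point holds as a minor one about precision and reproducibility. With 500 resamples, each 95% limit for between-group Cohen's d has a Monte Carlo SD of about 0.03 to 0.04, and 95% of seeds span about 0.12 to 0.17. Limits for within-group d vary less. The planned hypothesis tests, the sample size and the design are unaffected.

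The figures rest on a percentile bootstrap, normal-shaped data, 23 to 28 per arm, and d = 0.5 as the reading of a medium effect. A different bootstrap type or skewed scores would change the exact values, but the number of resamples in each tail would remain small.

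**What to change.** In Section 2.6, replace 500 with at least 10,000 bootstrap samples and state that the random seed will be recorded. At 23 per arm and d = 0.5 this lowers the Monte Carlo SD of the limits to about 0.01 (0.008 lower, 0.011 upper) and narrows the band holding 95% of seeds to about 0.03 to 0.04. The cost is one edited sentence and seconds of computing; participants, design and sample size are untouched.
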